The Safe Steps model has generated interest in mental health services across NSW, with training on the model recognised and recommended for implementation in other services. It has been further developed into a full programme that includes meaningful cultural consultation, peer and advocate involvement, and multi-professional input, as part of a multi-site translational research. Informing its further development is a range of knowledge bases on the value of therapeutic relationships, recovery, lived experience involvement, choice [36,37], trauma-informed care [38], mental health nursing emotional capabilities [38,39], mental health nurses’ professional identities [40,41], mental health nursing specialist education and training [42–44], and restorative approaches [45,46].

This protocol outlines a proposed series of studies evaluating the Safe Steps for De-escalation model, which was developed to address several gaps in the academic mental health literature. The model offers a structured approach to therapeutic responding, grounded in content, input, and participation from diverse key stakeholders, from intervention design, implementation, through to evaluation. The proposed evaluation addresses three core objectives and tests two overarching hypotheses. The first objective is to examine the effectiveness of the Safe Steps in reducing restrictive practice events, duration, and physical injuries. It was hypothesised that intervention units would show more significant reductions in IRR of restrictive practice events (defined as seclusion, physical restraint, and sedation via intramuscular injection [IMI]), estimates of restrictive practice duration (i.e., seclusion and physical restraint duration), and IRR of physical injuries, compared to control groups and within-group baseline. The second objective is to assess whether the Safe Steps improves people’s experience of services and perceived staff action on violence prevention, and nurses’ professional quality of life and demonstrated emotionally intelligent workplace behaviours. It was hypothesised that scores from these four measures at the final time point would be significantly higher than at baseline. Lastly, the third objective is to explore factors influencing the successful, pragmatic implementation of the Safe Steps.

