**Fig 2 pone.0325558.g002:**
[figure not shown]
Outcomes and data gathering timeline. CEO-MHS = Consumer Evaluation of Mental Health Services; EI = emotional intelligence; eMeds = electronic medication management system; IMI = intramuscular injection; ims+ = incident management system; ProQOL = Professional Quality of Life; VPC-M-FR = Modified Violence Prevention Climate.

There will be three forms of comparisons within the current evaluation. Between- i) and within-group ii) comparisons will be applied to test the first and second sets of hypotheses. The third will be a between-cluster comparison iii), intended to identify the most active co-occurring therapeutic and nursing responses (clusters) contributing to the Safe Steps’ overall impact. The first set of hypotheses is that implementation units will exhibit greater reductions in the IRR for restrictive practice events, the estimate of restrictive practice duration, and the IRR for physical injuries, compared to control groups and their baseline levels. The second set of hypotheses is that measures of service experience, perceived staff action towards violence prevention, nurses’ professional quality of life, and nurses’ perceived demonstration of emotionally intelligent workplace behaviours at the final time point would be significantly higher than at baseline. The between-group comparisons will be conducted exclusively to address the first objective, as these analyses will depend on accessible routine reports on restrictive practices and physical injuries selected for this purpose. Australian public acute mental health services are legally mandated to report on seclusion and physical restraint events and duration as key performance indicators [52]. Events of physical injuries and sedation via IMI are also routinely documented in established information management systems. These routine measures will help minimise performance and detection bias associated with the lack of blinding. Conversely, conducting a between-group comparison on non-routine measures could be cost-prohibitive and challenging to implement, as exemplified by unmet sample size requirements in previous studies [27]. This evaluation will have no randomisation, although covariate balancing will be applied to between- and within-group comparisons in testing the first set of hypotheses.

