### Sample

Outcome change measurement and qualitative research within the evaluation depend on two forms of samples: daily aggregates of observed events and individual and nurse participants. Daily aggregates of restrictive practice and physical injury events will be used to analyse these outcomes. In contrast to a ‘per incident’ level, an aggregated approach helps prevent the false impression of completeness [20]. It enables a more accurate evaluation of potential reporting biases in real-world data. On the other hand, people receiving care and nurse participants will be involved in the qualitative strand and survey-based measures.

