### Analysis plan

Quantitative and qualitative analyses will be used to answer the evaluation’s objectives. Consultations with statisticians occurred for the range of statistical treatments employed in this evaluation. Various packages in R [74] and RStudio [60] will be maximised for the quantitative analyses, and Matplotlib [75] will be utilised for visualising outcomes. Each hypothesis will be supported if outcomes are statistically significant at p < .05.

Poisson mixed-effects models [56] will be used for count data and linear regression models for continuous outcomes, to determine whether these outcomes differ according to intervention implementation and time points. Data cleaning and validation, assumption checks, model diagnostics, and follow-up analyses will be undertaken. Negative binomial mixed models, zero-inflated models, and linear mixed-effect models may be used depending on the model’s diagnostics. Covariates in the mixed-effect models will include the acute care unit, calendar month, day, year, and the day within the study period for each daily event aggregate. Model selection will prioritise parsimony and explanatory strength. Inverse probability weighting (IPW) will be applied in the between- and within-group comparisons. Using the ipw package [76], IPW will be used to balance covariates, including but not limited to the average harm scores of daily aggregates, the number of high observation beds, the number of seclusion rooms, and other confounds (i.e., physical restraint and Code Blacks are closely interrelated, influencing each other’s occurrence or implementation [77]). Listed covariates for balancing will be used, subject to the data’s fit and the statistical model’s ability to achieve convergence in the IPW approach.

Hierarchical clustering analysis [78] will support the emergence of co-occurring mental health nursing response clusters, which will then be the fixed effect in modelling differential associations with restrictive practices, physical injuries, and situational aggression. This cluster and regression analysis constitutes the between-cluster comparison to identify the most active response clusters contributing most to Safe Steps’ overall impact.

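### The weight model is to balance event variables that the intervention may change (harm scores and, on the plain reading, restraint and Code Blacks), with no limit to pre-implementation values

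*Protocol article*

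**What the plan says.** The Analysis plan section of the protocol article states that "Inverse probability weighting (IPW) will be applied in the between- and within-group comparisons". It then lists what the weights should balance: "IPW will be used to balance covariates, including but not limited to the average harm scores of daily aggregates", the numbers of high observation beds and seclusion rooms, and other confounds. A parenthesis explains the last item: "physical restraint and Code Blacks are closely interrelated, influencing each other’s occurrence or implementation". The list is conditional only on fit to the data and convergence of the weighting. Timing relative to implementation is not mentioned.

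The Design section confirms the role of the weights: "This evaluation will have no randomisation, although covariate balancing will be applied to between- and within-group comparisons", for the first set of hypotheses. The Sample section sets the unit of analysis: "Daily aggregates of restrictive practice and physical injury events will be used to analyse these outcomes".

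Two of the balancing variables are treated as outcomes elsewhere:

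- **Physical restraint.** The objectives at the end of the Introduction name, as the first target, "restrictive practice events (defined as seclusion, physical restraint, and sedation via intramuscular injection [IMI".
- **Code Black.** Table 1 lists it among the additional outcomes, the de-escalation log records it as an outcome, and Sample size gives it its own power calculation (10.8 months, 85.20% power). It is not part of the first hypothesis as worded.

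The harm score is not named as an outcome anywhere, and the article does not define it.

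**The concern.** Inverse probability weighting recovers a total effect only if the balanced variables are unaffected by the exposure. Safe Steps is meant to settle distress before it leads to a Code Black, restraint or harm. If implementation days are weighted until they match baseline or control days on those events, part of the change under test is weighted away.

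The reason given for including restraint and Code Blacks, that each influences the other, describes linked outcomes. It does not describe variables that precede the exposure.

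At stake is every weighted test of the first objective. The within-group comparison is the clearest case. Values on post-implementation days necessarily follow the intervention. Bed and seclusion-room numbers are presumably fixed within a unit, so the event variables are most of what remains to balance.

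**Working it through.** The protocol gives no figure for the effect of weighting, so there is nothing to reproduce. Daily event rates and the correlations between event types are not given either. The sizes below are therefore illustrations on stated assumptions.

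**Formulas.** Let A = 1 on implementation days and A = 0 on comparison days, and let p be the fitted probability that A = 1 given the balancing variables. With groups of equal size, the weight is 0.5/p when A = 1 and 0.5/(1 − p) when A = 0. The weighted IRR is the weighted mean daily count for A = 1 divided by that for A = 0.

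**A case checkable by hand (all inputs assumed).** Take 0.30 Code Blacks a day, a Code Black IRR of 0.70, and a restraint rate of 0.02 plus 0.35 per Code Black.

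- Comparison rate: 0.02 + 0.35 × 0.30 = 0.125.
- Implementation rate: 0.02 + 0.35 × (0.70 × 0.30) = 0.0935.
- True restraint IRR: 0.0935/0.125 = 0.75.
- Weighting on the Code Black count equalises that count, so both rates become equal and the IRR becomes 1.00 (simulated: 0.746 unweighted, 0.997 weighted).
- If about half the effect bypasses Code Blacks, the simulated IRR is 0.64 unweighted and 0.86 weighted.

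**A wider range.** The design was 3 units × 365 days in each condition, with no true confounding and 200 runs per setting. There were 0.5 or 1.0 conflict events per unit-day. Each event led to restraint, Code Black or seclusion with probability 0.3 to 0.6. The harm score was zero on event-free days and rose with the day's events. The intervention lowered the conflict rate. Of the true IRRs, 0.88 is the 12% reduction in Sample size, 0.37 is the seclusion result of the first implementation in the Introduction, and 0.60 is an assumed value between them.

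| Outcome; variables in the weights | True 0.88 | True 0.60 | True 0.37 |
|---|---|---|---|
| Seclusion; none | 0.87–0.88 | 0.60 | 0.37 |
| Seclusion; restraint, Code Black | 0.93–0.97 | 0.77–0.89 | 0.61–0.81 |
| Seclusion; restraint, Code Black, harm | 0.95–0.98 | 0.87–0.91 | 0.79–0.86 |
| Restraint; Code Black, harm | 0.96–0.97 | 0.84–0.90 | 0.77–0.85 |
| Restraint; restraint, Code Black, harm | 1.00 | 1.00–1.01 | 1.00–1.04 |

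**Direction.** In a second model, seclusion and restraint were linked only through patient agitation, with a true seclusion IRR of 0.60 and weights on restraint alone. The weighted IRR was 0.60 when restraint was unchanged, about 0.63 when restraint fell (rate ratio 0.8 or 0.6), and 0.58 when it rose (rate ratio 1.2).

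**Would baseline-only weights repair both comparisons?** Not the within-group one. A unit's baseline-year rate is the same number on its pre and post days. With 365 days in each period, p = 365/730 = 0.5 on every day, every weight is 0.5/0.5 = 1, and nothing is balanced. In the between-group comparison, three units against three give at most six distinct values of any unit-level quantity. The Setting section adds that the control units have no high observation areas, so separation is a real risk.

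**The case against.** The strongest defence is that this is a condensed article. It states an intent to balance accessible confounders, and the timing of covariates is often settled in a fuller plan. A year of baseline daily data exists from which suitable values could be drawn. That is fair as far as timing goes. But the article names the variables and the comparisons, and sets a condition on the list that has nothing to do with timing. Followed as written, it admits implementation-period values.

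Four stronger readings are tempting and not supported:

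- **That same-day values are stated to be used.** This is inferred from the harm score being taken from daily aggregates and from the daily unit of analysis. The text does not say it.
- **That all the balanced variables are outcomes.** The harm score is not a listed outcome. It is, on its description, a severity measure attached to the daily aggregates, so the objection to it is that implementation-period values may be affected by the intervention.
- **That restraint will be in the weights when restraint is analysed.** The parenthesis is loosely worded. Its plain reading is that "physical restraint and Code Blacks are closely interrelated" and are balanced on that account, but it does not say whether the analysed outcome is left out. If it is left out, the other variables still remain.
- **That an effective programme would be declared ineffective.** This is possible but not shown. The near-complete loss of effect in the hand example assumes that everything runs through Code Blacks. The simulations also omit the unit and calendar terms of the planned mixed models.

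**Conclusion.** The point holds in limited form. The plan lists event-related variables as balancing covariates for both comparisons and does not restrict them to the period before implementation. To the extent that Safe Steps changes them, the weighted IRR is not an estimate of its total effect. That conclusion needs no assumed rates; it follows from the covariate list and the outcome definitions.

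The direction is toward 1 if the intervention lowers these events, as the protocol hypothesises. The size is unknown. At the planning effect, the illustrations move a seclusion IRR of 0.88 to about 0.93 to 0.98. The effect on restraint is lost altogether only if restraint is both the outcome and a weighting variable. These figures rest on assumed event rates, strong links between event types and no confounding. With weaker links the shift was small, and it was absent or reversed when restraint did not fall.

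**What to change.** 1. **Weight model.** For every outcome under the first hypothesis, exclude harm scores, restraint counts and Code Black counts from the implementation period. Analyse restraint and Code Blacks only as outcomes.
2. **Between-group comparison.** Allow only fixed unit features or baseline-year quantities in the weights. Where weights cannot be estimated with three units against three, rely on the pre/post-by-group contrast in the mixed model, using the baseline year.
3. **Within-group comparison.** Drop the event-based weights and rely on the unit and calendar terms already planned for the mixed model, since unit-level baseline values cannot balance periods.

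The cost is a short amendment to the Analysis plan and some re-specification of the models. Recruitment and consent describes register, ims+ and eMeds data for the year before each site's start. It does not mention harm scores, and Procedures describes collection in the control units as prospective. Before the contrast in item 2 is fixed, the sponsor should confirm that baseline-year data are available for the control units, and should check the source of any baseline harm score.

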### Setting

The evaluation will be conducted across two NSW local health districts (LHDs). LHDs in NSW are health administrative regions with distinct budgets and governance under Australia’s universal healthcare framework, making up geographically based districts and three specialised networks. The intervention sites will consist of three declared adult mental health inpatient units, with a combined capacity of 75 beds, including ten designated for high observation. Operating 24 hours a day and situated within public hospitals, these units cater to varying levels of mental health treatment and observational needs. Delivering acute care from these units to people from different catchments and adjacent local government areas are peer workers and traditional staff from different disciplines, including but not limited to nurses and nurse educators. These units vary in local care models, restrictive practice rates, peer work involvement, and restrictive practice review approaches.

The control sites will be three declared adult inpatient units within two public hospitals in one LHD. Their total bed capacity is 84, and they are without high observation areas. Clinical input supported identifying these sites, considering the bed capacity and availability of high observation beds. One control site has no seclusion room, making it impossible to observe seclusion events or measure their duration. However, as detailed in the Analysis Plan section, the number of seclusion rooms and high observation beds will be considered for covariate balancing. Similar to the intervention sites, the three control units operate with varying levels of mental health practices and are multidisciplinary.

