The Safe Steps evaluation is robust. It contributes to the limited knowledge base that discerns the most active co-occurring responses contributing to a programme or multi-component intervention’s overall impact. A significant limitation of complex interventions aimed at reducing restrictive practices is determining which elements contribute most to the effect, particularly as the impact of nurses’ therapeutic responses has not been evaluated in isolation. Rather, it is usual to see before-and-after evaluations of training interventions on these responses [see 29,88]. Moreover, control groups and statistical adjustments will be applied to address the absence of randomisation. Given that recruiting appropriate control groups and controlling for confounds is a well-documented challenge in acute care reform [26], this approach that balances covariates enhances this evaluation’s validity. This evaluation includes outcomes, such as sedation via intramuscular injection and physical injuries, that are rarely examined in de-escalation training interventions [29], helping to expand understanding of key indicators for evaluating mental health service performance in Australia [90]. The Safe Steps implementation and evaluation features a year-long period, allowing for the identification of both emergent and sustained impacts. This extended timeframe contrasts with most Safewards studies, which typically span only a few months [27].

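### Weighting covariates are kept or dropped by model fit and convergence, not by achieved balance, so the stated balance between groups cannot rest on this rule

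*Protocol article*

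**What the plan says.** The Analysis plan section gives the purpose of the weighting: "IPW will be used to balance covariates". The covariates it lists are "the average harm scores of daily aggregates, the number of high observation beds, the number of seclusion rooms, and other confounds". It then makes their use conditional: "Listed covariates for balancing will be used, subject to the data’s fit and the statistical model’s ability to achieve convergence in the IPW approach".

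The Setting section describes the intervention units as "with a combined capacity of 75 beds, including ten designated for high observation". Of the control units it says: "Their total bed capacity is 84, and they are without high observation areas", and further: "One control site has no seclusion room, making it impossible to observe seclusion events or measure their duration". It then points to covariate balancing in the Analysis plan as the response to these differences.

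Two other places speak of balance without that condition. The Design section says that "covariate balancing will be applied to between- and within-group comparisons in testing the first set of hypotheses". The Discussion claims that "this approach that balances covariates enhances this evaluation’s validity".

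**The concern.** The purpose of the weights is balance, but the condition for using a covariate is that the weight model fits and converges. These are different properties, and here they pull apart. A group-membership model has trouble converging when a covariate predicts group perfectly or almost so, which is when the groups differ most on it. Conversely, a model can report convergence and still leave its own covariates unbalanced, and nothing in the clause would reject it.

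This is not a remote possibility. One listed covariate, high observation beds, is present in the intervention group and absent from every control unit. Another, seclusion rooms, is zero in one control unit. What is at stake is the description of the between-group result: it could be presented as covariate-balanced when the covariates the article itself singles out are either missing from the weights or still far apart after weighting.

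**Working it through.** The plan gives no figure to reproduce here, so the check asks what the rule does to the two unit-level covariates.

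**Inputs from the Setting section.** Three intervention and three control units; ten high observation beds against none; no seclusion room in one control unit.

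**Assumptions, because the article does not give them.** Beds per intervention unit 4/3/3, 5/5/0 or 10/0/0. Seclusion rooms 1/1/1 or 2/1/1 (intervention) against 1/1/0 (control). A logistic weight model on 6 units x 365 days, with at most 25 iterations and convergence declared at a relative deviance change below 1e-8. The fits also held a simulated daily harm score with a mean shift of 0.3 SD.

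**Formulas.** With p the fitted probability of being an intervention unit-day, the weight is 1/p in intervention units and 1/(1-p) in control units. The standardised difference is (weighted intervention mean - weighted control mean) / sqrt((v1 + v0)/2), where v1 and v0 are the unweighted group variances. Each unit contributes the same number of days, so days cancel and the limiting values can be checked by hand, leaving out the harm score.

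**Beds 4/3/3.** Beds separate the groups completely. The fit did not converge in 25 iterations and every weight was 1.0. Means 10/3 = 3.33 and 0; v1 = 0.222, v0 = 0; difference 3.33 / sqrt(0.111) = 10. The rule would drop this covariate.

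**Beds 5/5/0.** Of four units without such beds, one is an intervention unit, so p = 0.25 there and p tends to 1 where beds exist. Intervention weights 1, 1, 4. Mean (5 + 5 + 0)/6 = 1.67 against 0; v1 = 5.56; 1.67 / sqrt(2.78) = 1.0. The fit reported convergence at iteration 18.

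**Beds 10/0/0.** Two of five units without beds are intervention units, so p = 0.4. Weights 1, 2.5, 2.5. Mean 10/6 = 1.67 against 0; v1 = 22.2; 1.67 / sqrt(11.1) = 0.5. Convergence at iteration 17.

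**Rooms 1/1/1 against 1/1/0.** p = 3/5 where there is a room. Control weights 2.5, 2.5, 1, so the control mean is 5/6 = 0.833 against 1; v0 = 0.222, v1 = 0; 0.167 / sqrt(0.111) = 0.5. Convergence at iteration 17.

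**Rooms 2/1/1 against 1/1/0.** p = 0.5 at one room, tending to 1 at two and to 0 at none. Means 6/5 = 1.2 and 4/5 = 0.8; v1 = v0 = 0.222; 0.4 / sqrt(0.222) = 0.85. Convergence at iteration 18.

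| Covariate and assumed split | Converges? | Weighted standardised difference |
|---|---|---|
| Beds 4/3/3 | no | 10 |
| Beds 5/5/0 | nominally | 1.0 |
| Beds 10/0/0 | nominally | 0.5 |
| Rooms 1/1/1 v 1/1/0 | nominally | 0.5 |
| Rooms 2/1/1 v 1/1/0 | nominally | 0.85 |

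Convergence is nominal because no finite maximum likelihood estimate exists in these cases; the deviance merely stops changing.

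**If both covariates are left out.** The model with the harm score alone converged in 4 iterations and balanced that score (difference about 0), but left beds at 0.99 to 10 and rooms at 0.99 to 1.42. By the stated rule this is an acceptable weight model.

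**Independently of the split.** Every control unit-day has zero high observation beds, so the weighted control mean is 0 whatever the weights. Inverse probability weights are positive, so the intervention mean stays above 0. No weighting balances this covariate.

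**The case against.** The strongest reply has four parts.

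- **Removal is not certain.** A reader might infer that the covariates that differ most are bound to be dropped, or that such models never converge. The documents do not support that. The clause is conditional, the split of the ten beds by unit is not given, and in four of the five assumed scenarios the software criterion is met and the covariate could stay. This objection stands. What is left is that the rule fails either way, by dropping the covariate or by passing it unbalanced.
- **The effect on the estimate may be nil.** A reader might take the 12% reduction in the Sample size section, assume a 20% higher event rate in the intervention units, and read 0.88 x 1.20 = 1.06 as the distorted rate ratio. That holds only for a comparison of follow-up levels. The hypotheses concern greater reductions than in controls, and the models include time points and unit. A rate difference that is constant over time cancels in a change contrast: (1.20 x 0.88 / 1.20) / (1 / 1) = 0.88. The 20% also has no source in the article. No size of bias is claimed here.
- **Diagnostics may be in a fuller plan.** The article promises model diagnostics in general terms, and a missing balance table is no finding in itself. That is right, but the point concerns a rule the article does state, and a table elsewhere would not change the criterion for keeping a covariate.
- **The article hedges.** The Design section limits balancing to accessible covariates and leaves uncontrolled factors to qualitative explanation, and the Setting section discloses the bed and room differences. This softens the point without removing it: bed and room counts are accessible and are among those listed for balancing.

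**Conclusion.** The point holds in a limited form. The stated rule for keeping weighting covariates does not measure balance. In the between-group comparison it can discard a separating covariate (beds at 4/3/3) or accept one that remains unbalanced (0.5 to 1.0 for beds, 0.5 to 0.85 for rooms, against a customary limit of 0.1). These values rest on assumed unit splits, a logistic weight model and the convergence setting used. The statement that beds cannot be balanced rests only on the article's ten against none. The unconditional wording on balance in the Design and Discussion sections is therefore not supported by the rule.

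The within-group comparison is not affected by this example: bed and room counts that stay fixed within a unit do not separate baseline from follow-up. Nor does the check show that the effect estimate is biased, or by how much.

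**What to change.** Replace the convergence clause with a criterion of achieved balance on the listed covariates, measured before implementation: for example, a weighted standardised difference below 0.1, with the effective sample size reported. Show the result for every listed covariate, including any left out of the weight model.

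Report a covariate that prevents convergence or stays unbalanced as not balanced, and limit the wording in the Design and Discussion sections to match. In that case, base the controlled conclusion on the unweighted group-by-period contrast with unit terms. That contrast removes unit differences that are constant over time, though not differences in trend.

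The cost is a few sentences of plan wording and one table, with no new data. The downside is that some weighted results may have to be set aside; for high observation beds the article's own figures already show that the criterion will not be met.
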